### Follow-Up Assessments

Participants are assessed at 6 weeks and at 3, 6, 12, 18, and 24 months after completion of CT-STAR treatment. CTCAE v5.0-evaluated adverse events are reported at all of these time points, while patient-reported quality of life is ascertained via the European Organization for Research and Treatment of Cancer and EQ-5D-3L at 6 weeks and 3-, 6-, and 12-months after CT-STAR. Volumetric imaging and tumor response, both having occurred at baseline, are repeated at 3, 6, 12, 18, and 24 months posttreatment to determine the patients’ response to radiotherapy.

### Study End Points

The primary end point for ARTIA-Pancreas is the rate of acute (90 d) grade 3+ treatment-related GI toxicities as defined by the CTCAE v5.0 and compared to the historical rate of 20%. The trial’s key powered secondary end point is the rate of late (12-month) grade 3 or higher treatment-related GI toxicities as defined by the CTCAE v5.0 criteria and compared to the historical rate of 25%. Additional secondary end points include (1) a Kaplan-Meier estimate of the rates of overall survival at 12 and 24 months post completion of CT-STAR; (2) local (in-field) control rates at 12 and 24 months post completion of CT-STAR, defined as stable disease, partial response, or complete response by the Response Evaluation Criteria in Solid Tumors criteria; and (3) the Kaplan-Meier estimates of distant progression-free survival at 12 and 24 months post completion of CT-STAR.

Exploratory end points of ARTIA-Pancreas are listed in Table S1 in Multimedia Appendix 1.

### Statistical Analysis

#### Primary End Point

ARTIA-Pancreas is powered to the primary end point. It is hypothesized that CT-STAR will reduce the rate of CTCAE v5.0 grade 3+ GI toxicity compared to non-ART, where the historical acute toxicity rate is 20% or higher. It is hypothesized that using CT-STAR, the acute toxicity rate will be <10% for an effect size of 10% or more. A total of 107 evaluable participants (ie, participants with nonmissing data for the primary end point) are targeted. There must be ≤13/107 (12.1%; 95% CI 7.2%‐19.7%) participants with acute grade 3+ GI toxicity in the study. With this rule, the study’s 1-sided false positive error rate (α) is 0.023, and the power is 0.82. Given the possibility that participants could become eligible for surgical resection at the treated site following radiation, which would preclude toxicity assessment in those participants, we estimate a 20% attrition rate, and 134 participants will be targeted for enrollment.

CTCAE v5.0 grade 3+ GI toxicity compared to a historical rate of 20% will be analyzed by constructing a Wilson score 95% CI for the observed acute grade 3+ GI toxicity incidence rate. The CI’s upper limit being <20% will indicate rejection of the historical rate of 20% at a 1-sided *P*<.025 significance level (ie, success for the study’s primary end point).

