## Introduction

The only known curative intervention for patients with pancreatic cancer is surgical resection [1]. However, only approximately 20% of patients are clearly eligible for curative intent resection at the time of diagnosis, while 30% to 40% of patients present with either borderline resectable or locally advanced disease [2]. In patients with borderline resectable (BR) or locally advanced pancreatic cancer (LAPC), neoadjuvant chemotherapy and/or chemoradiotherapy are typically used for the purpose of tumor downstaging and affording the opportunity for curative resection [3]. Despite neoadjuvant treatment, only 20% to 30% of patients with BR/LAPC are typically converted to resectability, highlighting the need for improvements in these chemo- and radiotherapies to contribute to or provide definitive therapy [3]. Computed tomography (CT)–guided stereotactic adaptive radiotherapy (CT-STAR), a recent technological advancement in the radiotherapeutic space, may overcome the shortcomings of conventional radiotherapy to improve care for BR/LAPC.

Historically, conventional radiotherapy has shown only modest use in patients with pancreatic cancer, with randomized phase 3 clinical trials demonstrating a lack of survival benefit and only modest local control gains in patients treated with conventional chemoradiotherapy versus chemotherapy alone [4,5]. Dose-escalated conventional radiotherapy may convert 20% to 30% of unresectable patients to resectability [3] but imparts significant side effects, with rates of acute grade 3+ nonhematologic and gastrointestinal (GI) toxicity as high as 20% to 30% [3,4,6,7].

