Stereotactic body radiotherapy (SBRT), which leverages fewer treatment days and higher dose conformality compared to conventional radiotherapy, has emerged as an alternative approach for achieving local disease control in patients with pancreatic cancer. However, ablative CT-guided pancreatic SBRT has been shown to induce similarly (>20%) concerning rates of grade 3+ GI toxicity [8] when target coverage is prioritized over organ-at-risk (OAR) protection. In patients with unresectable pancreatic cancer, studies suggest that reducing treatment margins and building in constrained planning-organ-at-risk volumes may partly mitigate acute GI toxicity following ablative SBRT [9-11]. Even so, these approaches do not consistently lead to meaningful reductions in late GI toxicity [12] and/or result in intentional limitation of tumor coverage. Therefore, historical use of ablative SBRT has been limited to near-palliative dosing regimens [13] or to use in patients with highly selective anatomic presentations [9,10,14].

Online adaptive radiotherapy (ART), a form of radiotherapy in which interfraction changes to the radiation dosimetry plan are made in response to observed changes in tumor and OAR anatomy, has emerged as a feasible and safe mechanism to deliver ablative SBRT to patients with abdominal cancer [15,16]. In patients with tumor locations with direct OAR abutment or invasion that would traditionally preclude treatment with ablative SBRT, online adaptive planning and delivery may enable safe delivery of ablative SBRT [17]. Findings from both a small, multi-institutional retrospective analysis and a recent phase 2 clinical trial suggest that dose escalation enabled by ART may improve 2-year overall survival while reducing grade 3+ GI toxicity in patients with BR/LAPC [18-20]. Furthermore, single-institution series and prospective analyses indicate that daily ART with magnetic resonance (MR) guidance may allow for safe incorporation of elective nodal irradiation (ENI) volumes with ablative doses [21,22], which is desirable per current treatment guidelines [23], but historically limited due to concerns of toxicity [24,25].

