### Dose Prescription and Delivery Considerations

Radiotherapy treatment consists of SBRT delivered in 5 fractions once daily or once every other day in 1 to 2 weeks. Participants receive a planned dose of 50 Gy in 5 fractions to the PTV with 33 Gy in 5 fractions to the ENI volume, with strict OAR sparing of luminal GI OARs prioritized over target coverage.

An exhale breath-hold approach using ancillary, commercially available respiratory management systems is used for respiratory gating. At the time of treatment, an end-exhale breath-hold CBCT daily alignment image is acquired to establish a new reference threshold based on the daily anatomy. The participant’s respiratory motion is monitored using a respiratory trace generated and displayed to the treatment team for manually triggered breath-hold respiratory gating of radiation delivery. To monitor intrafraction participant motion, CBCT can be repeated a maximum of 10 times per fraction in the breath-hold position.

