### Anticipated Results

Enrollment for ARTIA-Pancreas began in May 2023 and is anticipated to yield clinical findings shortly after completion in February 2028. The trial will provide evidence as to whether ablatively dosed radiotherapy that is adapted to the daily anatomy of each patient with BR/LAPC will reduce GI side effects. If, as is hypothesized, CT-STAR can reduce rates of treatment-related GI toxicity in this population, it may provide a rationale for the safe and effective incorporation of ablatively dosed CT-guided ART as a standard-of-care therapy.

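### Rejecting the 20% benchmark cannot show a reduction compared with non-adaptive radiotherapy, because the article's own 20% figures come from treatment planned differently from this trial

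*Protocol article*

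**What the plan says.** In the protocol article, Statistical Analysis, Primary End Point, the hypothesis is a contrast with non-adaptive radiotherapy: "It is hypothesized that CT-STAR will reduce the rate of CTCAE v5.0 grade 3+ GI toxicity compared to non-ART, where the historical acute toxicity rate", a rate then given as 20% or more. For CT-STAR the expectation is that "the acute toxicity rate will be <10% for an effect size of 10% or more". The trial succeeds if the Wilson 95% upper limit is below 20%, which at 107 evaluable participants means 13 events or fewer. The stated one-sided alpha is 0.023 and the stated power 0.82.

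Under Anticipated Results, the trial is said to provide evidence on "whether ablatively dosed radiotherapy that is adapted to the daily anatomy of each patient with BR/LAPC will reduce GI side effects". The Discussion Overview likewise credits adaptive SBRT with the hypothesised fall from 20% to 10%.

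Three statements in the Introduction bear on where 20% comes from:
- Ablative CT-guided SBRT: "similarly (>20%) concerning rates of grade 3+ GI toxicity [8] when target coverage is prioritized over organ-at-risk (OAR) protection".
- Dose-escalated conventional radiotherapy: "with rates of acute grade 3+ nonhematologic and gastrointestinal (GI) toxicity as high as 20% to 30" per cent.
- Non-adaptive measures in SBRT: "reducing treatment margins and building in constrained planning-organ-at-risk volumes may partly mitigate acute GI toxicity following ablative SBRT".

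This trial delivers its dose "with strict OAR sparing of luminal GI OARs prioritized over target coverage" (Dose Prescription and Delivery Considerations). The planning section makes the OAR limits strict for the initial plan as well as the adapted ones, and gives up target coverage where needed to meet them.

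**The concern.** The test compares one arm with a fixed number. The hypothesis built on it concerns a treatment contrast, adaptive against non-adaptive. The step from one to the other holds only if 20% is a fair rate for non-adaptive treatment that is otherwise like the trial's treatment, in similar patients.

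The article does not support that. Its SBRT figure belongs to the opposite planning priority. Its conventional-radiotherapy figure describes the highest reported rates and includes nonhematologic toxicity, whereas the end point is treatment-related GI toxicity only. It also names a route to lower acute toxicity that needs no adaptation.

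At stake is what a positive result may be said to show. The 0.023 error rate guards against passing CT-STAR when its true rate is 20% or more. It does not guard against crediting adaptation when adaptation contributes nothing.

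**Working it through.** **Inputs** (Primary End Point section): n = 107 evaluable, cut-off 13, benchmark 20%, hypothesised rate 10%, attrition 20%.

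**Step 1: reproduce the plan's figures.**
- Wilson limits: [p + z²/2n ± z·√(p(1−p)/n + z²/4n²)] / (1 + z²/n), with z = 1.96. For 13/107 this gives 7.2% to 19.7%, as stated. For 14/107 the upper limit is 20.8%, so 13 is the correct cut-off.
- Alpha: P(X ≤ 13 | n = 107, p = 0.20) = 0.0233. Stated: 0.023.
- Power: P(X ≤ 13 | n = 107, p = 0.10) = 0.819. Stated: 0.82.
- Enrolment: 107 / 0.8 = 133.75, rounded up to 134, as stated.

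All of these reproduce. The arithmetic of the rule is not at issue.

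**Step 2: set the sources of 20% beside the trial.**

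| Feature | Sources in the Introduction | This trial |
|---|---|---|
| Planning priority (SBRT) | Coverage over OARs | OARs over coverage, in initial and adapted plans |
| Toxicity counted (conventional radiotherapy) | Nonhematologic and GI | Treatment-related GI only |
| Meaning of the conventional figure | Highest reported rates | Used as a floor for non-ART |
| Anatomy | Ablative SBRT largely confined to selected anatomy | Gross stomach or duodenal invasion excluded; adequate visibility on CBCT required |
| Elective nodal volume | Limited in the past because of toxicity concerns | Included, 33 Gy in 5 fractions |

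The first two rows could put the trial's rate below 20% without any effect of adaptation. The last row could push it up. The anatomy row could act in either direction.

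**Step 3: chance of success if adaptation does nothing.** Let p be the acute rate under non-adaptive SBRT with the same OAR limits in the same patients. The documents give no value, so p is an assumption. With no effect of adaptation, CT-STAR has the same rate, and the chance of success is P(X ≤ 13 | n = 107, p):

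| Assumed p | Chance of success |
|---|---|
| 20% | 0.023 |
| 18% | 0.07 |
| 16% | 0.17 |
| 15% | 0.25 |
| 13% | 0.47 |
| 12.5% | 0.53 |
| 12% | 0.59 |
| 10% | 0.82 |

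The chance reaches one half only at about 12.5% or below.

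**Step 4: the opposite direction.** Suppose instead that the like-for-like non-adaptive rate in these patients were 25%, and adaptation removed the 10 percentage points that the trial hopes for. CT-STAR would then have a rate of 25 − 10 = 15%, and the rule would succeed with probability only 0.25. The 25% is purely illustrative. It shows that the mismatch can also hide a real effect.

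**The case against.** The strongest reply is that the formal decision is already modest. The Primary End Point section defines success as rejecting a historical rate of 20%, and the Study Objectives section uses the same comparison. Limitations concedes the weaknesses of historical comparators in general, gives time confounding as an example rather than a full list, and points to future randomised trials. Anticipated Results is worded conditionally. All of this is true and keeps the point from being grave. Still, the general concession does not name the reversed planning priority, which is known now and built into the design, and the hypothesis and Anticipated Results still speak of non-ART and of adaptation.

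A second reply is that 20% is not a generous benchmark. It is the lower end of the conventional range quoted and below the SBRT figure, and the SBRT figure, the closer comparator, counts GI toxicity alone. This also stands. A reader might infer that the benchmark was taken from the top of a range. The text does not say so, and the point does not need it.

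Third, strict OAR limits may be hard to hold from day to day without adaptation, so the two may not separate cleanly in practice. That is reasonable, but it is an argument for expecting an effect. A single arm measured against 20% does not test it.

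**Conclusion.** The concern holds as a limit on inference. A pass would show that the acute grade 3+ treatment-related GI toxicity rate after OAR-prioritised CT-STAR is below 20%. It would not show that the rate is lower than with non-adaptive radiotherapy, or that adaptation is the cause. The direction of the bias is unknown.

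The size depends wholly on an assumed comparator rate: 0.07 at 18%, 0.25 at 15%, 0.59 at 12% and 0.82 at 10%, against the nominal 0.023.

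Three stronger readings are tempting but not supported:
- That the trial will usually succeed by default. This needs a non-adaptive OAR-first rate of about 12.5% or less, and the Introduction says only that such measures may help in part.
- That the 25% benchmark for late toxicity fails in the same way. The Introduction says the non-adaptive approaches do not reliably reduce late toxicity, so the mechanism argued here does not carry over.
- That the stated alpha or power is wrong. Both are right for the hypothesis actually tested.

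**What to change.** Keep the 107 evaluable participants, the cut-off of 13 and the 20% benchmark, and change the text:

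1. In Primary End Point, the Discussion Overview and Anticipated Results, restate the hypothesis and the permitted conclusion as: *the acute grade 3+ treatment-related GI toxicity rate after OAR-prioritised CT-STAR is below the 20% benchmark.* Do not attribute a pass to adaptation or to superiority over non-ART.
2. In Limitations, add that the SBRT figure above 20% comes from coverage-prioritised planning, whereas this trial prioritises OARs, so the comparison mixes adaptation with planning priority and patient selection.

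A table of toxicity by whether the adapted or the scheduled plan was delivered could be added as description only. The adapted plan is chosen when the scheduled plan breaks a constraint, so receiving it partly reflects unfavourable anatomy. Such a table is confounded by indication and could not carry a claim about adaptation.

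The two text changes need no extra participants, procedures or analyses. The price is a more modest headline claim.

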#### Key Secondary End Point

ARTIA-Pancreas is also powered to analyze the key secondary end point, contingent upon a positive result for the primary end point. For the key secondary end point, it is hypothesized that CT-STAR will reduce late GI toxicity from a historical rate of 25% or greater to less than 10%. Given an evaluable 107 participants, there must be 17 (15.9%) participants or fewer with late grade 3+ GI toxicity in the study to reject a 25% or higher CT-STAR toxicity. With this rule, the key secondary end point’s 1-sided false-positive error rate is 0.016 when the true late toxicity rate is 25%, and the power is 0.98 when the true late toxicity rate is 10%.

If the key secondary end point is indeed evaluated, a Wilson score 95% CI will be constructed for the study’s observed 12-month grade 3+ GI toxicity incidence rate. The CI’s upper limit being less than 25% will indicate rejection of the historical rate of 25% at a 1-sided *P* value less than .025 significance level (ie, success for the study’s key secondary end point).

#### Secondary End Points

Twelve- and 24-month overall survival as well as distant progression-free survival will be evaluated by Kaplan-Meier analysis. All other secondary end points will be descriptively summarized.

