### Comparison With Prior Work

The historical framework for the use of radiotherapy in BR/LAPC is summarized in the “Introduction” section. The current clinical paradigm favors the use of ablative doses of SBRT with a strategy focused on minimizing adverse effects to adjacent normal tissues using daily adaptive techniques. In the recent phase I and retrospective studies, MR-based ART has been reported to improve the therapeutic index of SBRT for BR/LAPC, with encouraging local control rates of 70% to 80% at 2 years following treatment and a favorable toxicity profile [32]. While MR provides high-quality radiotherapy planning images, MR-guidance platforms require special construction, zoning, training, and staff presence that may impede widespread access to ART. In addition, patients may have MR imaging–incompatible medical devices or surgical implants that adversely impact the ability to deliver MR-guided ART.

ARTIA-Pancreas evaluates CT-, rather than MR-, guided ART [21,22] in an appropriately powered prospective clinical trial. The commercially available, advanced kV-CBCT imaging technology used in ARTIA-Pancreas can perform large field-of-view scans in the time of a single breath-hold and has demonstrated clinically acceptable target delineation and OAR daily anatomy visualization. Should the primary hypothesis of ARTIA-Pancreas be met, CT-guided ART may become a solution that achieves both clinical performance and potentially more widespread availability.

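### Local control at 12 and 24 months is left to a descriptive status rate, so the result depends on how resected, deceased and unscanned participants are counted; a cumulative incidence would settle this

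*Protocol article*

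**What the plan says.** In the protocol article, Study End Points lists three additional secondary end points. Overall survival and distant progression-free survival are named there as Kaplan-Meier estimates. The third is a rate: "local (in-field) control rates at 12 and 24 months post completion of CT-STAR, defined as stable disease, partial response, or complete response", by RECIST.

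Statistical Analysis, Secondary End Points, keeps the same division: "Twelve- and 24-month overall survival as well as distant progression-free survival will be evaluated by Kaplan-Meier analysis". The next sentence is "All other secondary end points will be descriptively summarized". Of the three, only local control falls under it.

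On who can be assessed, the Primary End Point section notes that "participants could become eligible for surgical resection at the treated site following radiation, which would preclude toxicity assessment in those participants", and continues: "we estimate a 20% attrition rate, and 134 participants will be targeted for enrollment". This is said of toxicity, not of local control. The only definition of an evaluable participant, in the same section, is for the primary end point. Data Collection, Management, and Monitoring rules out imputation of missing outcomes and describes sensitivity analyses for toxicity only. Follow-Up Assessments schedules imaging and tumor response at 3, 6, 12, 18 and 24 months.

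**The concern.** A RECIST status at month 12 or 24 exists only for a participant who is alive, has been scanned and still has a lesion at the treated site to assess. In this population many will not meet those conditions. A status rate then has several possible denominators, and each answers a different question:

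- A proportion among those assessed conditions on having survived and not been resected.
- A proportion among all enrolled counts death or resection without local failure as loss of control.
- Counting resected participants as controlled gives a third figure.

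Time-to-event methods address this, and the article uses one for the two neighbouring end points but not for this one.

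The figure will be read closely. Dose Prescription and Delivery Considerations puts sparing of the luminal organs ahead of target coverage, so low toxicity could partly reflect reduced coverage. Local control is the listed secondary end point that would show it.

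**Working it through.** **Plan's own figures.** The article states no expected local control rate, so there is none to reproduce. Its enrollment figure does reproduce: 107 / (1 − 0.20) = 133.75, rounded up to 134.

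**Step 1. Resection only, no deaths.** Inputs: 134 enrolled and 20% attrition, from the article. Assumption: all the attrition is resection, and resected participants have no later RECIST status at the treated site. Then 0.20 × 134 = 26.8, or 27 resected, leaving 107. The number controlled among the 107 is chosen for illustration, at about 70% and about 80%.

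| Counting rule | 75 of 107 controlled | 86 of 107 controlled |
|---|---|---|
| Resected excluded | 75/107 = 70.1% | 86/107 = 80.4% |
| Resected counted as not controlled | 75/134 = 56.0% | 86/134 = 64.2% |
| Resected counted as controlled | 102/134 = 76.1% | 113/134 = 84.3% |

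The same data move by about 20 percentage points with no survival assumption.

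**Step 2. Deaths.** The article gives no survival or local-failure assumption, so these inputs are mine: constant monthly hazards of local failure λ = 0.015 and of death before local failure μ = 0.025, and a death hazard after local failure of mμ with m = 1, 2 or 3. Resection is left out of this step.

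Formulas at month t:

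- Alive and controlled: A = exp(−(λ+μ)t)
- Alive after local failure: F = λ[exp(−(λ+μ)t) − exp(−mμt)] / (mμ − λ − μ)
- Survivor-only proportion: A/(A+F)
- Kaplan-Meier with deaths censored: exp(−λt)
- One minus cumulative incidence, death competing: 1 − [λ/(λ+μ)][1 − exp(−(λ+μ)t)]

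At 24 months A = exp(−0.96) = 0.383.

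- m = 1: F = 0.015 × (0.3829 − 0.5488)/(−0.015) = 0.166; survivor-only = 0.383/0.549 = 69.8%.
- m = 2: F = 0.015 × (0.3829 − 0.3012)/0.010 = 0.123; survivor-only = 0.383/0.505 = 76%.
- m = 3: F = 0.015 × (0.3829 − 0.1653)/0.035 = 0.093; survivor-only = 0.383/0.476 = 80.4%.
- Kaplan-Meier: exp(−0.36) = 69.8%.
- One minus cumulative incidence: 1 − 0.375 × 0.617 = 76.9%.

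The last two do not depend on m. The survivor-only figure does: for fixed local-failure and pre-failure death hazards, it rises as death after local failure becomes more frequent.

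At 12 months with m = 3: A = exp(−0.48) = 0.619 and F = 0.015 × (0.6188 − 0.4066)/0.035 = 0.091. Survivor-only is 0.619/0.710 = 87%, one minus cumulative incidence is 1 − 0.375 × 0.381 = 86%, and Kaplan-Meier is exp(−0.18) = 84%.

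**Step 3. What the choice about resection does within a time-to-event estimate.** Return to Step 1 with 32 of the 107 failing locally, and suppose all 27 resections come before any failure. With resection as a competing event, one minus cumulative incidence is 1 − 32/134 = 76.1%. With censoring at resection, Kaplan-Meier gives 1 − 32/107 = 70.1%. The two still differ, but each has a stated meaning.

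**The case against.** The strongest reply is that the article never writes of a simple proportion. A descriptive summary fixes no denominator, and for an unpowered secondary end point such detail commonly sits in the full protocol or the analysis plan. That stands as far as the missing denominator goes; its absence alone would not be a point. What the article does fix is the method: it names Kaplan-Meier for two of the three end points, in two places, and assigns the third to a descriptive summary. An unseen plan could add a denominator, but to supply a time-to-event estimate it would have to go beyond the published method.

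Three stronger readings are tempting, and the document does not support them.

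- A reader might infer from Step 2 that the reported figure could lie anywhere from 38% to 80% at 24 months. The 38% is alive and controlled over all enrolled. The article never proposes that denominator for local control, and its rule against imputing missing outcomes points away from it. The span also comes from one assumed set of hazards.
- A reader might infer that a survivor-only proportion must flatter the treatment. In the illustration this depends on the assumed rise in mortality after local failure. With no rise it equals Kaplan-Meier (69.8%), and even with a tripled hazard it is within 4 points of one minus cumulative incidence.
- A reader might infer that the result could not be compared with the "encouraging local control rates of 70% to 80% at 2 years following treatment" cited for MR-guided treatment. The article does not say how that figure was calculated, and it plans no such comparison.

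It is also fair that the statement about resection concerns toxicity. The article does not say that local status becomes unobtainable. Step 1 takes that as an assumption.

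**Conclusion.** The point holds in a limited form. The article assigns local control a weaker method than its neighbours, and the resulting rate depends on how resected, deceased and unscanned participants are counted. The firmest measure of size is the resection example: 56%, 70% or 76% from the same data. It uses the article's 134 and 20%, and assumes that resection accounts for all the attrition and removes later RECIST status.

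The further effect of deaths at 24 months rests wholly on assumed hazards: survivor-only about 70% to 80%, against 77% by one minus cumulative incidence. At 12 months the gap between survivor-only and time-to-event estimates is small, about 84% to 87% with a tripled hazard.

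Local control has no hypothesis, threshold or power, and neither toxicity conclusion depends on it. The change is worth making because it is cheap and makes the figure interpretable, not because the trial's success is at risk.

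**What to change.** In Study End Points and in Secondary End Points, replace the descriptive rate with the cumulative incidence of local (in-field) failure at 12 and 24 months after CT-STAR, in all treated participants, with 95% CIs. Date failure from the scheduled scans. Treat death without local failure as a competing event. Treat resection as a competing event in the main analysis, and censor at resection in a sensitivity analysis; censoring alone would not do, because participants who become resectable are probably not a random subset. Keep the table of stable disease, partial response and complete response as supportive, with its denominator stated.

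The cost is wording and a little extra analysis. No scans are added, since imaging at 3, 6, 12, 18 and 24 months is already planned, and the sample size does not change.
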